We will combine the data already extracted, stored and cleaned from APTS with the additional data obtained from study sites for each participating baby, to determine which factors are most influential in reducing transfusion requirements. The specific objectives are, after adjustment for prior risk factors (listed below), to determine:

1. Whether the effect of the intervention (cord clamping) on the outcome (blood transfusions) is mediated by placental transfusion (measured by hematocrit (Hct)) as seen in Figure 1 (a, c) following the causal path X → M1 → Y, where X is the intervention, ICC or DCC, Y is the outcome, mediator M1 is placental transfusion, and M2 is initial severity of illness stability

2. Whether the effect of the intervention (cord clamping) on the outcome (blood transfusions) is mediated by initial severity of illness (respiratory support, sampling line yes/no and total duration number, blood pressure, cumulative blood sample volume) as seen in Figure 1 (b, c) following the causal path X → M2 → Y

3. Whether the effect of cord clamping intervention on the outcome (blood transfusions) is driven by multiple mediators (placental transfusion and initial severity of illness) as seen in Figure 1 (c)

4. Whether cording clamping intervention (ICC or DCC) has a direct effect on the outcome after accounting for the mediators as seen in all panels of Figure 1: X → Y.

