The intervention consisted of either immediate or delayed cord clamping (as assigned in APTS). Immediate clamping was defined as clamping the cord within 10 seconds of delivery. Delayed clamping was defined as clamping the cord at least 60 seconds after delivery, with the infant held as low as possible, below the introitus or placenta, and with no palpation of the cord. Variations in the protocol were allowed if they would aid the mother, baby, or both. If the baby was non-vigorous (heart rate <100 beats per minute, low muscle tone, or lack of breathing, or crying), clinicians were allowed to break protocol using their discretion. Cord milking was not part of the protocol for either intervention. Further details may be sourced from the original APTS publication [15].

Outcomes

The primary outcome is the proportion of babies receiving red cell transfusion (for restoration of hemoglobin or blood volume). The secondary outcomes are number of transfusions per baby, cumulative transfusion volume (mL/kg) per baby, and primary reasons for each transfusion.

Putative Mediators

M1: Indicators of placental transfusion to be assessed will be hematocrit (on admission, highest on the first day, highest in the first week collected before any postnatal transfusion).

M2: Indicators of initial severity of illness to be assessed will be cumulative blood sample volume collected throughout hospital stay (number of blood tests multiplied by hospital’s usual sample volume for each type of test), sampling line (umbilical arterial line or peripheral arterial line) - yes/no and total duration, mechanical ventilation or inspired O2, and blood pressure.

Sensitivity Analyses (For the Primary Outcome Analysis Only)

Sensitivity analyses will adjust for the following variables: gender, birth <27 weeks vs. ≥27 weeks, method of delivery (vaginal versus cesarean), intraventricular hemorrhage (IVH) (yes/no and grade III/IV yes/no), surgery for patent ductus arteriosus (PDA), necrotizing enterocolitis (NEC), and sodium in the first 24 hours of life. We will also test model assumptions relating to sequential ignorability and post-randomization confounding (discussed further in the data analysis plan).

Potential Confounders (Covariates)

The following covariates may be used for adjustment in the analysis: gestational age at randomization before birth and any oral iron supplement pre-transfusion.

Timing of Assessments

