3.5	ICC / DCC	remaining Hct variables*	Blood pressure	Transfusions any/vol/n

Sensitivity analyses have been limited to a set of biologically plausible and clinically meaningful groups that will be explored by including them for adjustment with covariates, and with the introduction of interaction terms if appropriate. Missing data will be described, reasons for missing data will be explored, and the impact of missing data on conclusions about the treatment effect on the primary outcome will also be explored where possible (e.g., using sensitivity analyses and multiple imputation techniques).

Methodological Assumptions

The causal mediation approach assumes sequential ignorability: that the treatment effect on the outcome is not confounding and that the mediator effect on the outcome is not confounded. As treatment was randomly allocated to neonates, we will assume that the treatment-mediator relationship is not confounded. However, the mediator itself has not been randomized. Thus, unknown confounders may be driving a spurious effect in the mediator-outcome relationship. We will employ additional sensitivity analyses to estimate whether any mediation effects are sensitive to the violation of the assumption of sequential ignorability. To test the possibility of unmeasured confounders we will examine the correlation between residuals in the mediator model and the outcome model. If there is no correlation this would suggest there is no unmeasured confounding, if there is correlation between the residuals, an unmeasured mediator may be affecting both the measured mediator and the outcome. We will apply the method developed by Imai et al. and Tingley et al. [23,26] that uses sensitivity analyses to evaluate if the ACME estimate is sensitive to unmeasured confounding.

Post-randomization confounders are dependent on the treatment allocated, affect both mediator and outcome, and can corrupt the mediation estimate. In the context of the present trial, it is possible that non-adherence to the intervention is a post-randomization confounder. We are analyzing our data based on intention to treat principles; however, a sensitivity analysis based on the actual time of cord clamping to assess the influence of non-adherence with the treatment protocol on our estimates may be performed.

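### Oral iron before transfusion, one of two permitted covariates, is defined by the timing of the outcome; the sensitivity analyses also adjust for complications and sodium that arise after clamping

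*Protocol article*

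**What the plan says.** The Objectives section frames every question this way: "The specific objectives are, after adjustment for prior risk factors (listed below), to determine". The section on potential confounders then states "The following covariates may be used for adjustment in the analysis" and names two items: gestational age when randomized, and "any oral iron supplement pre-transfusion".

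The section on sensitivity analyses, limited to the primary outcome, adds sex, gestation group, method of delivery and intraventricular hemorrhage (IVH), followed by "surgery for patent ductus arteriosus (PDA), necrotizing enterocolitis (NEC), and sodium in the first 24 hours of life". The Data Analysis Plan says that these variables are entered alongside the covariates, with interactions if appropriate.

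The estimands are the average causal mediation effect (ACME), the average direct effect (ADE) and the average total effect. Under Timing of Assessments, mediators must have been measured before the outcome. No such rule is set for covariates.

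Methodological Assumptions gives the relevant warning: "Post-randomization confounders are dependent on the treatment allocated, affect both mediator and outcome, and can corrupt the mediation estimate". The only candidate it then names is non-adherence to the allocated clamping time.

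**The concern.** Clamping takes place within 10 seconds of delivery in one arm and at 60 seconds or later in the other. Oral iron, IVH, ductus surgery, necrotizing enterocolitis (NEC) and first-day sodium all arise or are measured after that. None of them is a prior risk factor in the sense of the Objectives.

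Iron is the sharper problem because its definition refers to the outcome. Adjusting for it partly conditions on when, and whether, the baby was transfused. Table 1 also chooses between single- and multiple-mediator models by a test of independence after covariate adjustment, so iron could enter that decision too.

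The complications and sodium raise a different problem. If they follow from initial severity of illness (M2) or from clamping, adjusting for them blocks part of the effect under study. If they share unmeasured causes with transfusion, it can also open a new biasing path. A sensitivity analysis built this way can make genuine mediation look fragile.

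**Working it through.** The protocol states no figure for this point, so there is nothing to reproduce. The check has three steps; all numerical inputs in steps 2 and 3 are assumptions.

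**1. Timing.**

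| Variable | Fixed before clamping? | Required to precede the transfusion? |
|---|---|---|
| Gestational age, sex, delivery method | yes | yes, by nature |
| Oral iron before transfusion | no | yes, but the outcome closes the window |
| IVH, ductus surgery, NEC | no | no rule stated |
| Sodium in first 24 hours | no | no rule stated |

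**2. Iron with no effect on transfusion.** Let T be the time of first transfusion, H the horizon and S the day iron starts. The covariate equals 1 if iron is given and S < min(T, H). The standardized risk difference (DCC minus ICC) from a logistic model is compared with and without it.

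*Setting A:* constant hazard, H = 60 days, 90% receive iron, S normal with SD 5 days.

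| ICC / DCC risk | Mean iron start | Without iron | With iron | Shrinkage |
|---|---|---|---|---|
| 50 / 45% | day 14 | -0.049 | -0.043 | 1 - 0.043/0.049 = 12% |
| 60 / 54% | day 14 | -0.061 | -0.053 | 13% |
| 60 / 54% | day 28 | -0.062 | -0.042 | 32% |
| 60 / 50% | day 28 | -0.100 | -0.065 | 35% |
| 70 / 63% | day 28 | -0.070 | -0.045 | 36% |

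In the third row, iron exposure is 58.9% under ICC and 62.8% under DCC, and 89% of babies without iron are transfused. Both patterns come from the definition alone.

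*Setting B:* early-loaded first transfusions (Weibull shape 0.6), H = 70 days, risks 65% and 55%. With 70% to 90% uptake and mean start between day 14 and day 28, shrinkage is about 14% to 44%. With 100% uptake around day 28, the risk difference goes from -10.3 to -4.5 points, or 1 - 4.5/10.3 = 56%. In that case every baby without iron has been transfused, so the logistic model separates; it is a degenerate case.

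**3. A post-birth variable C as an ordinary covariate.** Take a linear model, all error variances 1, with C entered in both the mediator and the outcome model:

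- M = -0.3X + error
- C = cM + uU + kX + error
- Y = -0.1X + 0.5M + 0.5U + error, with U unmeasured

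The true values are ACME = -0.3 × 0.5 = -0.15 and ADE = -0.10. After adjustment for C:

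- X→M coefficient: -0.3 - [c/(c² + u² + 1)] × (-0.3c + k)
- M→Y coefficient: 0.5 - c × 0.5u/(u² + 1)
- ADE: -0.1 - k × 0.5u/(u² + 1)

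| Case | Adjusted ACME | Adjusted ADE |
|---|---|---|
| C affected by neither X nor M (c = 0, u = 0.5, k = 0) | -0.15 | -0.10 |
| C follows M (c = 0.3, u = 0, k = 0) | (-0.3/1.09) × 0.5 = -0.138 | -0.10 |
| C follows M (c = 0.5, u = 0, k = 0) | (-0.3/1.25) × 0.5 = -0.12 | -0.10 |
| Also shares a cause with Y (c = 0.5, u = 0.5, k = 0) | -0.25 × 0.4 = -0.10 | -0.10 |
| X also affects C (c = 0.5, u = 0.5, k = -0.2) | -0.183 × 0.4 = -0.073 | -0.1 + 0.2 × 0.2 = -0.06 |

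Simulation with one million records gave the same values to within about 0.001. Adjustment is harmless in the first case and distorts the estimates in the others.

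**The case against.** Five points on the other side have weight.

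- **Iron is permitted, not required.** The initial models contain only intervention and mediator. This stands: bias in the main analysis is conditional on the covariate being used.
- **The complications and sodium enter sensitivity analyses of the primary outcome only.** This stands. They affect how robustness is read, not the main estimate.
- **The Introduction reports no difference in other adverse outcomes**, in the parent trial or in the latest systematic review. A direct effect of clamping on IVH or NEC may therefore be small. This stands, but a path through M2 remains possible.
- **Some of these variables may be real confounders.** M2 includes blood sample volume accumulated over the whole stay. NEC or IVH can drive both that sampling and transfusion, so simply dropping them would leave confounding in place. This stands and shapes the fix.
- **The plan undertakes to test for post-randomization confounding.** The methods it describes are residual correlation, sensitivity of the ACME to unmeasured confounding, and a possible analysis by actual clamping time. None of these deals with measured post-birth variables used as covariates.

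A reader might infer that all five variables corrupt the main analysis, or that adjustment removes the effects. The protocol does not support that: the iron wording is permissive, the other four are confined to sensitivity analyses, and step 3 shows no change when neither arm nor mediator affects the variable. Nor should the 56% shrinkage be taken as a likely size. It rests on universal iron uptake and a separating model, and it treats the reduction of about 10% in the Discussion as absolute, which the text does not say.

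**Conclusion.** The point holds in a limited form. Oral iron before transfusion contradicts the Objectives' own description of what is adjusted for. Because its exposure window is cut off by the outcome, using it biases the effects even if iron does nothing. The direction is typically towards a smaller total effect, illustratively by about 12% to 44%. That range rests on assumed transfusion risks, iron timing and uptake, none of which the protocol gives.

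For IVH, ductus surgery, NEC and sodium, the conclusion concerns interpretation. After ordinary adjustment for variables that may follow from the mediators or occur after the transfusion, a change in ACME or ADE cannot be read as lack of robustness. Its size is unknown. No calculation specific to sodium was made. Sex, gestation and delivery method are not at fault.

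**What to change.** - Delete oral iron from the covariate list.
- State that conventional adjustment in the mediation models is limited to variables fixed before clamping: gestational age, sex and method of delivery.
- Do not enter IVH, ductus surgery, NEC or first-day sodium as ordinary covariates. Report them by arm.
- Where one of them precedes both the mediator and the transfusion and may confound the two, treat it as a treatment-affected confounder. The interventional-effects approach cited in the Data Analysis Plan can serve; there it is tied only to correlated mediators, so its use would need to be extended. Require timing information for these variables, as is already done for mediators.

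The first two changes are wording only and need no new data. The cost is a shorter adjusted sensitivity set and some extra analysis work where a complication has to be modeled as a treatment-affected confounder.

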Putative mediating variables will only be analyzed if they have been measured before the outcome and will be excluded if there is not adequate time and date information available. If the multiple mediator model is applied, careful consideration of timing information will be evaluated. If there is insufficient empirical information to conclude the causal ordering of mediators (M1 causes M2), we will adjust our analytic approach (as discussed in the analysis plan) and discuss any limitations.

Data Analysis Plan

The analysis will include all babies who were initially randomized in the APTS trial for whom we were able to obtain the relevant data and be based on intention-to-treat. All statistical analyses will be conducted in R version 4.1.3 (2022-03-10; R Foundation for Statistical Computing, Vienna, Austria). Descriptive characteristics for continuous data will be presented as means or medians, as appropriate, and categorical data will be presented as frequencies and percentages.

A model-based inference approach will be applied to estimate the average causal mediation effect (ACME), average direct effect (ADE), and the average total effect as recommended [23-25]. This approach will be applied with the R “mediation” package [26]. We will initially fit two models, one model with mediation as the dependent variable and intervention as the independent variable (mediator model), and a second model with the outcome as the dependent variable, and both mediation and intervention as independent variables (outcome model). To account for the clustering of multiples, estimates will be calculated with generalized estimating equations with a compound symmetric correlation structure to account for within subject correlations. Depending on the outcome (binary, count, skew) these will be modelled with the appropriate family and link functions.

A counterfactual framework will be applied to the mediator and outcome models to simulate the values of the mediator and outcome to estimate the potential values of the mediator. This process is used to estimate the ACME, ADE, and average total effects; 95%CI will be estimated with 1000 bootstrap simulations.

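### The correlation between fitted mediator-model and outcome-model residuals says nothing about unmeasured confounding, so the plan should not read a null result as reassurance

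*Protocol article*

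**What the plan says.** The Data Analysis Plan of the protocol article sets up two regressions. In the mediator model, the mediator is regressed on the intervention. The outcome model is described as "a second model with the outcome as the dependent variable, and both mediation and intervention as independent variables". The mediator is thus the response in the first and a predictor in the second. On estimation, "estimates will be calculated with generalized estimating equations with a compound symmetric correlation structure". Families and links are to be chosen to suit each outcome, whether binary, count or skewed. The primary outcome is binary (section Outcomes: "The primary outcome is the proportion of babies receiving red cell transfusion").

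Under Methodological Assumptions the article accepts that the mediator was not randomized and that a mediator-outcome association may be spurious. It then offers a test for unmeasured confounders: "we will examine the correlation between residuals in the mediator model and the outcome model". The reading of the result is fixed in advance: "If there is no correlation this would suggest there is no unmeasured confounding". A non-zero correlation is to be read as a hint of an unmeasured variable acting on both mediator and outcome. The next sentence adds, without any condition, a published sensitivity analysis of the ACME. The type of residual and the threshold for calling a correlation absent are not stated.

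**The concern.** Confounding of mediator and outcome is the main threat to a mediation analysis, because randomization protects only the effects of the intervention. The information on such confounding lies in the correlation between the unobserved errors of the two equations. The plan looks instead at the fitted residuals. A regression that contains the mediator chooses the mediator coefficient so that nothing correlated with the mediator is left over. Confounding therefore enters that coefficient, and with it the ACME, and leaves little or no trace in the residuals.

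At stake is how the results are described. The study exists to separate two mechanisms, and the Introduction ties the answer to whether an early top-up transfusion might be justified. A near-zero residual correlation, reported with the stated reading, would give a mechanism support that it has not earned.

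**Working it through.** The plan gives no figure on this point, so there is none to reproduce. The check consists of algebra and a simulation.

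**Inputs.** From the documents: the two model specifications, the exchangeable GEE and the binary primary outcome; 1401 babies (Recruitment and data collection), which is an upper bound for the analysis set. Assumed: one measured covariate C, the same in both models unless stated; 175 twin pairs; an unmeasured confounder U of strength c on both mediator and outcome.

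**Algebra.** Let W hold the intercept, the intervention X and the covariates. The mediator residual is e_M = M - Wa. The outcome model has regressors (W, M) and response residuals e_Y = Y - fitted Y. Least squares, and the score equations of logistic and Poisson regression, give

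- W'e_Y = 0 and M'e_Y = 0,
- hence e_M'e_Y = M'e_Y - a'W'e_Y = 0 - 0 = 0.

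Both residuals have mean zero because of the intercepts, so their correlation is zero whatever the confounding.

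**Where the confounding goes.** In the linear case, let the errors have standard deviations s_M and s_Y and correlation rho. The fitted mediator coefficient then tends to (true effect) + rho × s_Y / s_M. The data identify only this sum. Rho has to be assumed; it cannot be estimated from the fit.

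**Simulation, binary outcome.** M = 0.3X + 0.4C + cU + error; logit P(Y = 1) = -0.2X - 0.5C + bM - cU; 100 replicates per row. The fitted coefficient, response residuals and deviance residuals come from ordinary logistic regression with a linear mediator model. The GEE column uses exchangeable GEE for both models, with response residuals.

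| True effect b | Confounder strength c | Fitted mediator coefficient | Response residuals: largest absolute r | GEE: largest absolute r (smallest p) | Deviance residuals: mean r (runs with p<0.05) |
|---|---|---|---|---|---|
| 0 | 0 | -0.004 | 1.2e-15 | 0.0043 (0.872) | -0.0005 (0%) |
| 0 | 1 | -0.460 | 4.3e-16 | 0.0037 (0.890) | -0.0749 (100%) |
| 0 | 2 | -0.708 | 7.4e-16 | 0.0023 (0.931) | -0.1248 (100%) |
| -0.8 | 0 | -0.799 | 7.8e-16 | 0.0028 (0.916) | -0.0774 (100%) |
| 0.7 | 1 | 0.181 | 3.7e-16 | 0.0046 (0.865) | 0.0343 (0%) |

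The response-residual and GEE columns do not tell the confounded rows from the unconfounded ones. Over all GEE settings run with response residuals, the largest absolute correlation was 0.006, and the smallest p-value examined for the binary outcome was 0.83.

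**Other fits.**
- Linear mediator and linear outcome: largest absolute r about 2e-15, while a true coefficient of 0 was estimated as -0.18, -0.47 and -0.78 at strengths 0.5, 1 and 2.
- Binary mediator with logit models (as for sampling line yes/no, model 2.2 in Table 1): largest absolute r below 0.001, while the false mediator effect reached p<0.05 in 51%, 100% and 100% of runs at those strengths.

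**When the correlation is not near zero.**
- Deviance residuals follow the fitted mediator coefficient, whatever its source. Rows 2 and 4 show nearly the same signal, once from confounding alone and once from a real effect alone. Row 5 is confounded, and no run reached p<0.05.
- Unequal covariates (C in the mediator model only, linear outcome): r = 0.15 with p<0.05 in 100% of runs and no unmeasured confounder. At strength 1 it fell to 0.063 (88% of runs), and at strength 2 to 0.024 (no run).

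**Leaving the mediator out of the outcome model** gives residual correlations of -0.19, -0.49 and -0.79 at strengths 0.5, 1 and 2 when the true effect is 0. That quantity mixes a real mediator effect with confounding, so it is not a valid test either.

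**The case against.** The best defence is that the sentences describe, loosely, the sensitivity parameter rho: residuals stand for errors, and zero error correlation does mean no confounding in that framework. The surrounding paragraph is about sensitivity analysis and ends by naming such a method. But the article announces a test, says that the correlation of residuals from the two models will be examined, and attaches a conclusion to each result. That describes an empirical check on fitted quantities. If rho was meant, the wording still needs to change.

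Three other points stand and limit the concern:

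- A reader might infer that the correlation will always be zero. The documents do not support this. Exact zero needs the conditions given in the algebra, whereas the plan uses GEE, leaves links and residual type open, and includes a binary mediator.
- A reader might infer that the plan will therefore declare every model free of confounding. This does not follow either. The wording is hedged, no later step depends on the check, and the ACME sensitivity analysis applies whatever the check shows. The Results section promises to report the sensitivity analyses.
- The false coefficients above measure confounding under assumed strengths. That bias would exist without the check; the fault of the check is that it cannot reveal it.

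That the article condenses a longer plan does not help here, because the rule is stated and not merely omitted.

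**Conclusion.** The rule is wrong as written. Because the outcome model contains the mediator, the correlation of fitted residuals is uninformative about unmeasured mediator-outcome confounding. It is exactly zero in the standard case and practically zero under the planned GEE. Where it differs from zero, it reflects model form, a real mediator effect or an omitted measured covariate, and not specifically an unmeasured confounder. Both halves of the stated interpretation therefore fail.

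The algebra depends on no assumed number. The GEE bound of 0.006 does: it rests on the assumed twin share, effect sizes and confounder strengths, and stronger correlation within twin pairs would move the value somewhat further from zero without making it informative.

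Severity: should be fixed. No estimate or model changes, and a suitable sensitivity analysis is already in the plan.

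**What to change.** Under Methodological Assumptions:

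1. Delete the sentence that introduces the residual correlation and the sentence that interprets it.
2. State that absence of unmeasured mediator-outcome confounding cannot be tested from these data.
3. Base all statements on robustness on the planned ACME sensitivity analysis, and describe it as varying an assumed error correlation rho. One useful summary is the value of rho at which the ACME reaches zero; the exact output can be left to the full analysis plan.

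The cost is a few sentences. No new data are needed, and no analysis beyond the one already planned.

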**Figure 1 FIG1:**
[figure not shown]
Diagrams of the possible causal mechanisms for the outcome (Y) based on the cord clamping intervention (X) (a) A single mediator model in which the intervention X (intervention – ICC or DCC) affects the outcome Y through the indirect path of the mediator M1 (placental transfusion) and via a direct path from X to Y. In this model, M1 is assumed to be independent of M2; (b) An independent mediator model in which the intervention X (intervention – ICC or DCC) affects the outcome Y through the indirect path of the mediator M2 (initial severity of illness stability) and via a direct path from X to Y. In this model, M2 is assumed to be independent of M1; (c) If M1 is not independent of M2 the assumptions of models (a) and (b) are violated and we need to instead apply a multiple mediator model in which the intervention (X) affects the outcome (Y) through both mediators (M1 and M2) and via a direct path X to Y. In model (c) it is assumed that M1 has an acyclic relationship with M2, i.e., M1 causally influences M2. Careful consideration is needed to determine the sequential ordering of this relationship, this is discussed in the data analysis plan. ICC: immediate cord clamping; DCC: deferred cord clamping Image credit: study author; concept from Imai and Yamamoto [21] and Lee et al. [22]

Ethical considerations

The protocol was approved by the Northern Sydney Local Health District Human Research Ethics Committee in November 2019 (Version 3.0, Reference 2019/ETH12819), the Mater Misericordiae Ltd Human Research Ethics Committee (Version 1.0, Reference HREC/MML/56247), the Mercy Health Human Research Ethics Committee (Version 2.0, Reference 2020-078), and the Southern Health and Disability Ethics Committee (Version 1.0, Reference 19/STH/195). The ethics committees have granted a waiver of consent. The study is conducted in accordance with the National Health and Medical Research Council Statement on Ethical Conduct in Research Involving Humans.

Study measures

Intervention

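### Condition at birth can shorten clamping in the deferred arm and so confounds hematocrit with transfusion; intention to treat protects the total effect but not the mediation effects, and no planned model adjusts for it

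*Protocol article*

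**What the plan says.** M1 is placental transfusion (hematocrit) and M2 is initial severity of illness, as labelled in Objectives, Figure 1 and Table 1.

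- **Study measures, Intervention.** For one arm: "Immediate clamping was defined as clamping the cord within 10 seconds of delivery". The definition for the other arm reads: "Delayed clamping was defined as clamping the cord at least 60 seconds after delivery". Discretion to depart from allocation was tied to the baby's state: "If the baby was non-vigorous (heart rate <100 beats per minute, low muscle tone, or lack of breathing, or crying), clinicians were allowed".
- **Methodological Assumptions.** Post-randomization confounders are described as able to corrupt the mediation estimate, and "it is possible that non-adherence to the intervention is a post-randomization confounder". The response is: "We are analyzing our data based on intention to treat principles", with an analysis on actual clamping time that, "to assess the influence of non-adherence with the treatment protocol on our estimates may be performed". The section also plans a residual-correlation check and commits to an ACME sensitivity analysis for unmeasured confounding.
- **Potential Confounders and Sensitivity Analyses.** The candidate covariates are gestational age and oral iron. The listed sensitivity adjustments are sex, gestation group, mode of delivery, intraventricular hemorrhage, ductus surgery, necrotizing enterocolitis and early sodium. None measures condition at birth.
- **Figure 1 legend.** "In model (c) it is assumed that M1 has an acyclic relationship with M2, i.e., M1 causally influences M2". Timing of Assessments and the Data Analysis Plan allow a change of approach if the order cannot be established, or if M1 and M2 appear correlated without one causing the other.

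**The concern.** The protocol identifies non-adherence as a threat to the mediation estimate but not what drives it. Its own intervention text supplies the driver. A baby allocated to deferral who is not breathing or has a low heart rate may be clamped early. Such a baby plausibly receives less placental blood and is also more likely to become ill and be transfused. In the immediate arm, clamping is due within 10 seconds, so there is little room for condition to shorten it. The result is a mediator-outcome confounder largely confined to one arm. It is also a common cause of M1 and M2.

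Randomisation balances condition at birth between arms, which protects the total effect. It does nothing for the association of hematocrit with transfusion within the deferred arm, and the ACME and ADE are built from that association. The likely direction is to credit placental transfusion with risk that belongs to condition at birth. The Introduction draws implications for early top-up transfusion from exactly this contrast, so a bias towards M1 matters.

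**Working it through.** The plan states no figure to reproduce. The check is whether the bias exists under the plan's own structure, how large it could be, and whether the planned safeguards would catch or remove it.

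**Inputs from the document** (Introduction; Recruitment and data collection): hematocrit difference by allocation 2.7 points; risk difference for any transfusion -0.07; 1401 babies.

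**Assumed, not in the document:** proportion non-vigorous p = 0.30; probability q = 0.5 or 0.9 that a non-vigorous baby in the deferred arm is clamped early (15% or 27% of the arm); within-group hematocrit SD s = 5 to 7; lack of vigour adds g = 0.20 or 0.40 to transfusion risk; overall transfusion risk 0.58; vigour affects hematocrit only through clamping; **hematocrit has no effect on transfusion**, so the true ACME is 0.

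**Closed form (linear product of coefficients)**

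- Gain if clamping is actually deferred: e = 2.7 / (1 - pq)
- Covariance of hematocrit and transfusion in the deferred arm: C = -e · g · p(1 - p)q; in the immediate arm it is 0
- Hematocrit variance in the deferred arm: V = s² + e² · pq(1 - pq); in the immediate arm it is s²
- Common slope given arm: b = C / (V + s²); false ACME = 2.7 · b

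With s = 5, g = 0.20, q = 0.9: e = 2.7/0.73 = 3.70; C = -3.70 × 0.20 × 0.189 = -0.140; V = 25 + 13.68 × 0.197 = 27.7. The deferred-arm slope is -0.140/27.7 = -0.0050 per point and the common slope is -0.140/52.7 = -0.00265. The false ACME is 2.7 × -0.00265 = -0.0072, or 10% of -0.07. Simulation with 2 million babies gave -0.0071.

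| s | g | q | False ACME (formula) | Simulated | Share of -0.07 (formula) |
|---|---|---|---|---|---|
| 7 | 0.20 | 0.5 | -0.0018 | -0.0021 | 3% |
| 7 | 0.20 | 0.9 | -0.0038 | -0.0039 | 5% |
| 5 | 0.20 | 0.5 | -0.0035 | -0.0035 | 5% |
| 5 | 0.20 | 0.9 | -0.0072 | -0.0071 | 10% |
| 6 | 0.40 | 0.5 | -0.0049 | -0.0050 | 7% |
| 6 | 0.40 | 0.9 | -0.0101 | -0.0103 | 14% |

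In every row the total effect stayed at about -0.070 and the immediate-arm slope at about 0. The deferred-arm slope ran from -0.0015 to -0.0073 in simulation.

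A harsher set assumed that 20 to 30% were non-vigorous and **all** were clamped early, a 4 to 5 point hematocrit gain from actual deferral, SD 5 to 6, and an odds ratio of 2.7 to 4.5 for transfusion. It gave ACMEs of -0.0065, -0.0113 and -0.0134 against totals of -0.071, -0.067 and -0.066: shares of 9%, 17% and 20%.

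**Would the planned safeguards help?**

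- *Residual correlation.* The mediator residual is a linear combination of hematocrit, arm and the shared covariates. The outcome model contains all of these, so its residuals are orthogonal to the mediator residual. In linear and logistic fits with independent observations and the confounding present, the correlation was zero to machine precision. Working-correlation weights for multiples would blur the exact zero but do not make the check informative. The plan would read a zero as no unmeasured confounding.
- *Actual clamping time.* The simulated total effect became -0.104 to -0.218 instead of -0.070 in the scenarios with no hematocrit effect. The ACME in that analysis was near 0 there, but only because vigour was made to act on hematocrit solely through clamping. The total and direct effects, and hence any share mediated, were wrong.
- *ACME sensitivity analysis.* It shows how much confounding would overturn the ACME but does not correct it. A single overall residual correlation also fits a one-arm confounder poorly.

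**After adjustment.** With vigour in both models, the simulated ACME returned to about 0. It returned to about -0.027 in scenarios where that was the truth.

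**The case against.** The strongest reply is that the plan already does much of this. It never claims that intention to treat removes the confounding. It says plainly that the mediator was not randomised and that the mediator-outcome relation may be spurious, and it commits to an ACME sensitivity analysis. A reader might infer that intention to treat is its only answer; the document does not support that. What stands is that none of the stated measures adjusts for the driver that the protocol itself describes.

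A reader might also infer that early clamping of sick babies reverses the assumed order of M1 and M2. The listed M2 indicators are ventilation or oxygen, sampling lines, blood pressure and sample volume. None is vigour before clamping, so no listed M2 variable is shown to act on M1. Vigour is a common cause, which makes the order ambiguous and no more. Nor is the fallback confined to non-causal correlation: Timing of Assessments has a wider trigger. That trigger rests on timing information, however, and measurement times would not reveal a cause that precedes both mediators.

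A third inference is that the severity pathway is understated by the same amount. That was not shown. In the calculation, what the ACME gained the ADE lost (for example -0.063 instead of -0.070).

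Finally, the size may be modest. Departure was permitted, not required. Taking the overall risk of 0.58, the sampling SD of the ACME at n = 1401 is roughly 2.7 × √(0.58 × 0.42) / (s√1401): 0.7 points for s = 5 and 0.5 for s = 7, ignoring clustering. With half of the non-vigorous babies clamped early, the tabulated bias (0.2 to 0.5 points) is below one such SD. This limits urgency but does not remove a bias of predictable direction.

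**Conclusion.** The concern holds in this form: condition at birth is a plausible mediator-outcome confounder, largely confined to the deferred arm, that the planned models leave unadjusted. The total effect is safe; the ACME and ADE for hematocrit are not. If hematocrit had no effect, about 3 to 20% of the total effect could be credited to it. The upper end requires every non-vigorous baby in the deferred arm to have been clamped early, which the document does not say. All sizes depend on assumed rates of non-vigour and early clamping, an assumed link of vigour with transfusion, and assumed hematocrit SDs. The structural point does not depend on those values. It requires only that condition at birth influenced clamping and also predicts transfusion.

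**What to change.** In Methodological Assumptions, state that intention to treat protects the total effect but does not remove confounding of hematocrit with transfusion by condition at birth.

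For models 1.x and 3.x, prespecify a sensitivity analysis that:

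- keeps arm as randomised;
- adds a recorded measure of condition at birth to both the mediator and outcome models, preferably one assessed before clamping or otherwise least affected by arm;
- allows the hematocrit slope to differ by arm.

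Interpret the M1 effect according to whether it persists. Label any clamping-time analysis as confounded by condition at birth, and do not read a zero residual correlation as evidence of no confounding.

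The choice of measure needs care. Resuscitation before clamping is not comparable when one arm is clamped within 10 seconds, and a recorded reason for departure exists only for babies who departed. A score taken after clamping may itself be affected by arm, so it needs that caveat.

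The cost is one added analysis, slightly wider intervals, and possibly a few more items from hospital records already under review. The document does not show which of these items were recorded.
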